### Participant Timeline

This feasibility trial consisted of an 8-week intervention treatment phase, including 4 visits; the last 2 weeks will be a follow-up phase, and visit 4 will be performed remotely. The total trial data collection period will be 2 months. The measurements were performed as shown in Table 1.

### Sample Size

As this was a feasibility study, a sample size calculation is not required. However, we can estimate the number of participants we will be able to recruit during the data-collection period. In this feasibility study with a statistical power of 0.8, an α of .05, and an effect size of 1.20, the minimum required sample size will be 60 participants (30 in each group). Sample size calculations are estimated using G*Power (version 3.1.9.2).

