## Methods

### Overview

The Adhera CARINAE Digital Health Program will be tested in a multicenter trial, including 5 clinical settings across 3 European countries, and will use a stratified randomized controlled design including 30 intervention participants (6 per clinical site) and 30 control group participants (6 per clinical site; Multimedia Appendix 5). This study aimed to obtain objective answers to the following 2 research questions:

Is the designed protocol feasible for conducting a future definitive randomized controlled trial? Accordingly, to what extent does the program affect patients’ and caregivers’ stress, anxiety, and pain levels, and secondarily, well-being and overall quality of life, compared with patients receiving the standard of care only?What is the overall usability of the digital health solution based on the experience of patients, caregivers, and HCP?

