#### Randomization and Allocation

Participants-patients will be randomized through the prestratified randomization method to achieve balance between the 2 groups (intervention and control groups) according to the type of surgery and baseline characteristics (covariates). Stratified randomization was achieved by generating a separate block for each combination of covariates and participants were assigned to the appropriate block of covariates. The specific covariates in the clinical trial were represented by the type of surgery (3 surgeries) and sex (2 levels: male and female). With these 2 covariates, the possible block combinations totaled 6 (eg, male, cardiac valve replacement). According to this, the participants’ allocation will be blinded through an Excel file spreadsheet (RAND function) using permuted block randomization with a ratio of 1:1 between the intervention and control groups. Allocation concealment will be ensured, as we will not release the randomization code until the patients are recruited for the trial.

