### Data Analyses

The analyses will be conducted in Python 3.9.5 through the IDE PyCharm Community Edition 2021.2.1 Software and intention-to-treat principles. Descriptive statistics will be used to characterize the groups during the 4 visits. Furthermore, owing to the small sample size, Spearman correlations will be performed with all the variables to check, first, for potential associations between the variables and, second, differences between the intervention versus control groups. Further potential differences between these groups will be analyzed as follows:

Stress (VAS), pain (VAS), and mood state (PANAS-short form) will be subjected to a multivariate mixed analysis of variance (split-plot ANOVA) with “time” as a within-subject factor (ie, 4 time points) and “group” as a between-subject factor (intervention vs control).Patient activation (PAM-13) and self-efficacy (GSE-SF) will also be submitted to a multivariate mixed analysis of variance with “time” as a within-subject factor (Ie, 3 time points) and “group” as a between-subject factor (intervention vs control).Mental well-being (Short Warwick Edinburgh Mental Well-Being Scale) and HRQoL (EQ-5D-3L and EQ-5D-Y) will be analyzed using multivariate mixed analyses of covariance. As measurements of these 2 variables are based on a pre-post design, postmeasurements will be used as the dependent variable and premeasurements as covariates.

Finally, it is of interest to explore the effects as a function of different types of surgery. To this end, 2 different statistical approaches will be used:

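### The stated sample size does not follow from its inputs: an effect of 1.20 at 80% power needs about 12 per arm, while 30 per arm corresponds to about 0.74 SD

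*Protocol article*

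**What the plan says.** The Sample Size section opens with "As this was a feasibility study, a sample size calculation is not required". It then turns to how many participants can be recruited, and goes on to give a finished calculation: at power 0.8 and α .05, with "an effect size of 1.20, the minimum required sample size will be 60 participants (30 in each group". The software is named: "Sample size calculations are estimated using G*Power (version 3.1.9.2". The section does not give the test, its sidedness, the endpoint, the effect-size metric, a dropout allowance or a multiplicity adjustment.

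The same total appears in the Methods Overview as "30 intervention participants (6 per clinical site) and 30 control group participants (6 per clinical site", that is, 12 patients at each of five sites. Randomization and Allocation specifies "permuted block randomization with a ratio of 1:1 between the intervention and control groups". For stress, pain and mood, Data Analyses plans a "multivariate mixed analysis of variance (split-plot ANOVA) with “time” as a within-subject factor (ie, 4 time points", with group as the between-subject factor.

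**The concern.** A standardised difference of 1.20 is very large, and very large effects need few patients. A requirement of 30 per arm at only 80% power is therefore implausible on sight. Because the section prints inputs, output and software, the claim can be checked directly, and the fact that this is a feasibility study does not exempt it.

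The trial also plans inference between groups. Its first research question asks how far the program changes stress, anxiety and pain compared with standard care, and whether the protocol can support a later definitive trial. A reader who trusts the Sample Size section will believe that 60 patients can reliably detect only a 1.2 SD effect, and that a 1.2 SD effect requires 60 patients. If both beliefs are false, null and positive results will be misread, and anyone who reuses the pairing of 1.20 with 60 for planning will carry the error forward.

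**Working it through.** **Inputs.** Power 0.80, α 0.05, effect size 1.20 and 30 per arm come from Sample Size; 1:1 allocation comes from Randomization and Allocation. Two assumptions are needed because the article is silent: the test is two-sided, and 1.20 is Cohen's d (difference divided by SD). Both are relaxed below.

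**Attempt to reproduce 30 per arm.** The normal approximation is

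n per arm = 2(z₀.₉₇₅ + z₀.₈₀)² / d² = 2(1.960 + 0.842)² / 1.20² = 15.70 / 1.44 = 10.9, so 11.

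The exact calculation uses the noncentral t distribution with df = 2n − 2 and noncentrality d√(n/2):

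| n per arm | noncentrality | critical t | power at d = 1.20 |
|---|---|---|---|
| 11 | 2.81 | 2.086 | 76.3% |
| 12 | 2.94 | 2.074 | 80.2% |
| 30 | 4.65 | 2.002 | 99.5% |

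The exact solution is n = 11.94, so 12 per arm and 24 in total. The stated 30 is not reproduced; 30/12 = 2.5.

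**Other readings of the stated inputs.**

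| Reading | Required size |
|---|---|
| One-sided t test | 10 per arm (exact 9.34) |
| Rank test, two-sided (relative efficiency 0.955 or 0.864) | 13 or 14 per arm |
| Bonferroni for 3 primary outcomes | 17 per arm |
| Bonferroni for 36 tests | 26 per arm |
| 1.20 as Cohen's f, between-group or factorial ANOVA | 8 to 16 in total |
| 1.20 as Cohen's f, mixed ANOVA, 2 groups × 4 times | 4 to 8 in total |
| f = 0.6 (equivalent to d = 1.2), between-group or factorial ANOVA | 24 to 42 in total |
| f = 0.6, mixed ANOVA, correlation 0 to 0.9 | 4 to 24 in total |

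Dropout alone would have to be 1 − 12/30 = 60% to turn 12 into 30.

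**Routes that do reach 60.** Each one adds or changes an input:
- Power of 0.995 instead of 0.80 gives 30 per arm.
- A one-sided test with 10 per arm in each of three surgery types gives 30 per arm.
- An effect of f = 0.12 instead of 1.20, for the group-by-time interaction over four time points with an assumed correlation of 0.7, gives 60 in total (power 81.4%; 79.9% at 58).

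The article states none of these.

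**What 30 per arm provides** (two-sided, unadjusted, one time point):
- Detectable difference at 80% power: d = 0.736. If attrition left 27 or 25 per arm (assumed), it would be 0.78 or 0.81.
- Power at d = 0.5: 47.8%. Power at d = 0.3: 20.8%.
- 95% CI half-width: t₀.₉₇₅,₅₈ × √(2/30) = 2.002 × 0.258 = 0.517 SD.

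A one-sided test would put the detectable difference at 0.65.

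**The case against.** The strongest reply is that the calculation may be under-described rather than wrong. Randomization and Allocation stratifies by three surgeries, and Data Analyses plans separate analyses by surgery. A one-sided test at d = 1.20 needs 10 per arm (power 82.5%; 78.5% with 9), and three times 10 is 30. This could be where the figure came from. It does not rescue the sentence, which gives 60 as one overall requirement and mentions neither a one-sided test nor a calculation per surgery. It also fits the site plan poorly. With 6 per arm at each site, and the three types read as cardiac (two sites), urological cancer (one) and orthopaedic (two), the groups have 12, 6 and 12 per arm. The one-sided power with 6 per arm is 61%.

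A second point stands as a qualification. The 0.74 SD figure describes an unadjusted comparison at one time point, whereas the planned models use repeated measures or baseline adjustment. With an assumed baseline correlation of 0.3 to 0.7, multiplying 0.736 by √(1 − r²) gives 0.70 to 0.53. That moves the true figure further from 1.20.

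Third, the consequence is limited. The error is in the safe direction for an effect of 1.20, recruitment is complete, and no patient number or analysis changes. Whether 1.20 would be carried into a later trial is not known. All of this is true and argues for a small remedy, but it does not make the printed figure right. Nor does the remark that no calculation was needed: once a figure is presented as a computed minimum, it has to follow from its inputs.

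**Conclusion.** The concern holds. The printed inputs do not give 60. They give 12 per arm (24 in total) for a two-sided t test with 1.20 as Cohen's d, and 10 per arm if one-sided. Conversely, 30 per arm has 99.5% power for 1.20 and 80% power for about 0.74 SD (0.65 if one-sided). The exact figures depend on the assumed test, sidedness and metric, but the mismatch does not: among the readings tried, 60 appears only when an input is added or changed. Either 60 is not the minimum for 1.20, or 1.20 is not the effect for which 60 was chosen. The sample size can stand; the sentence justifying it has to be corrected.

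**What to change.** Delete the statement that ties 1.20 to 60. If the size was in fact set by what the sites could recruit, replace it with: *The sample size of 60 (30 per arm, 12 per site) was set by feasibility. It gives a 95% CI half-width of about 0.52 SD for a between-group difference, before baseline adjustment, and 80% power (two-sided α .05) for a difference of about 0.74 SD.*

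If the sponsor did use another calculation, state its test, sidedness, effect-size metric, any correlation assumed and whether it applies overall or per surgery type, so that a reader can reproduce 60.

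The cost is one corrected sentence. No patients are added, and neither the design nor the analysis changes.

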### Recruitment

#### Participants

Clinical investigators will prescreen the eligibility of the participants that they have available in their pool of subjects proposed for one of the surgeries in the inclusion criteria. Whenever they find a potentially eligible participant, they will invite them to participate in the study, either by phone or during routine consultation, whichever is more convenient. If the patient shows interest in participating in the study, then he or she will be referred to the research coordinator of the study that will facilitate him or her the patient information letter and the informed consent form and will solve any questions and concerns the patient may have. Upon obtaining informed consent, the patients will be considered recruited for the trial.

#### Randomization and Allocation

Participants-patients will be randomized through the prestratified randomization method to achieve balance between the 2 groups (intervention and control groups) according to the type of surgery and baseline characteristics (covariates). Stratified randomization was achieved by generating a separate block for each combination of covariates and participants were assigned to the appropriate block of covariates. The specific covariates in the clinical trial were represented by the type of surgery (3 surgeries) and sex (2 levels: male and female). With these 2 covariates, the possible block combinations totaled 6 (eg, male, cardiac valve replacement). According to this, the participants’ allocation will be blinded through an Excel file spreadsheet (RAND function) using permuted block randomization with a ratio of 1:1 between the intervention and control groups. Allocation concealment will be ensured, as we will not release the randomization code until the patients are recruited for the trial.

### Data Analyses

The analyses will be conducted in Python 3.9.5 through the IDE PyCharm Community Edition 2021.2.1 Software and intention-to-treat principles. Descriptive statistics will be used to characterize the groups during the 4 visits. Furthermore, owing to the small sample size, Spearman correlations will be performed with all the variables to check, first, for potential associations between the variables and, second, differences between the intervention versus control groups. Further potential differences between these groups will be analyzed as follows:

Stress (VAS), pain (VAS), and mood state (PANAS-short form) will be subjected to a multivariate mixed analysis of variance (split-plot ANOVA) with “time” as a within-subject factor (ie, 4 time points) and “group” as a between-subject factor (intervention vs control).Patient activation (PAM-13) and self-efficacy (GSE-SF) will also be submitted to a multivariate mixed analysis of variance with “time” as a within-subject factor (Ie, 3 time points) and “group” as a between-subject factor (intervention vs control).Mental well-being (Short Warwick Edinburgh Mental Well-Being Scale) and HRQoL (EQ-5D-3L and EQ-5D-Y) will be analyzed using multivariate mixed analyses of covariance. As measurements of these 2 variables are based on a pre-post design, postmeasurements will be used as the dependent variable and premeasurements as covariates.

Finally, it is of interest to explore the effects as a function of different types of surgery. To this end, 2 different statistical approaches will be used:

Cluster analyses per surgery type. Data will be split for each of the surgeries, and variables will be analyzed individually using time and group as within and between factors, respectively.A different statistical approach from the approach described above will also be used. In this case, analyses are performed within a linear mixed model (LMM) framework. LMM allows for the flexible handling of unbalanced data, outliers, or missing observations without averaging the data of participants. In addition, LMM enables the modeling of data using different fixed and random factors. Accordingly, each of the variables will be submitted to an LMM analysis wherein “time,” “group (intervention vs control)” and their interaction (time × group) will be included as fixed factors. In contrast, “subjects” and “surgery” will be submitted as random factors. This analysis enables the calculation of regression estimation parameters by considering that participants differ in the surgery type. In addition, the participants’ age or sex may also be used as control covariates.

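### Stress, pain and mood each get two tests of the same group effect, a complete-record split-plot ANOVA and a mixed model that keeps partial records, and the plan does not say which one decides

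*Protocol article*

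**What the plan says.** All statements here are from the Data Analyses section of the protocol article unless another section is named.

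- Principle: the analyses follow "Software and intention-to-treat principles".
- First group model for stress and pain (both primary) and mood (secondary): "Stress (VAS), pain (VAS), and mood state (PANAS-short form) will be subjected to a multivariate mixed analysis of variance (split-plot ANOVA"), with time entered "as a within-subject factor (ie, 4 time points") and group as the between-subject factor.
- Later, a new aim is introduced: "Finally, it is of interest to explore the effects as a function of different types of surgery". It continues: "To this end, 2 different statistical approaches will be used". The first approach splits the data by surgery. The second opens with "A different statistical approach from the approach described above will also be used" and is a linear mixed model.
- That mixed model is to be fitted to each variable. Its fixed factors are time, group and their interaction, and its random factors are subject and surgery.
- The stated reason for using it: "LMM allows for the flexible handling of unbalanced data, outliers, or missing observations without averaging the data of participants".
- HADS, listed as a primary outcome in Table 1, appears in none of the ANOVA or ANCOVA bullets.

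**The concern.** A classical split-plot ANOVA needs a value at every level of the within-subject factor. Without imputation, one missed questionnaire removes a randomised patient from the whole analysis, even if that patient never withdrew. If the three scales are analysed jointly, a gap in any one of them has the same effect. The protocol recognises missing observations as a reason to use a mixed model, but places that model under a secondary question.

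Two things are at stake. First, the complete-record patients may be a selected subset, and in any case there are fewer of them. Second, every ANOVA outcome receives two tests of one effect, possibly on different patients. With no stated precedence, the more favourable result can be put forward.

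**Working it through.** **1. The plan's own figure.** Sample Size gives 60 participants (30 per group) for power 0.8, α .05 and effect size 1.20. Read as a standardised mean difference with a two-sided t test, that effect size needs 12 per group, so the figure of 30 is not reproduced. This point does not depend on that mismatch: 30 per arm is taken below as the planned number. With 30 per arm, the difference detectable with 80% power is 0.74 SD.

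**2. The two models side by side.**

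| | Split-plot ANOVA | Linear mixed model |
|---|---|---|
| Listed for | difference between groups | exploration by surgery type |
| Outcomes | stress, pain, mood (other scales in a second bullet) | each variable, so HADS as well |
| Effect of interest | time × group | time × group |
| Surgery | not in the model | random factor, no group × surgery term |
| Patients used (no imputation) | all visits complete | any patient with at least one measurement |

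Without a group × surgery term, the mixed model cannot show whether the effect differs by surgery. It gives an overall group effect adjusted for surgery, which is the effect that the ANOVA tests.

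**3. Patients retained.** The protocol gives no missing rate, so the rate m per visit is assumed, with misses independent across visits. The share with all four visits is (1 − m)^4.

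- m = 5%: 0.95^4 = 0.815, about 24 of 30 per arm.
- m = 10%: 0.90^4 = 0.656, about 20 of 30 per arm.
- If baseline is always complete, the exponent is 3: 0.95^3 = 0.857 and 0.90^3 = 0.729, about 26 and 22 per arm.

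**4. Detectable effect.** Two-group comparison at one time point, two-sided α .05, 80% power, noncentral t:

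| Patients per arm | Detectable difference (SD) |
|---|---|
| 30 | 0.736 |
| 27 (all records kept at one visit, m = 10%) | 0.777 |
| 24 | 0.826 |
| 20 | 0.909 |

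With baseline complete, the values are about 0.80 SD (m = 5%) and 0.87 SD (m = 10%).

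**5. Bias.** Assume no true effect, a correlation of 0.6 between visits, and 15% to 20% of patients lost after admission. In the intervention arm, the log odds of loss rise by 1 per SD of admission stress. In controls, loss is either unrelated to stress or has slope −0.5.

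- Mean admission stress among intervention completers shifts by −0.13 SD (15% lost) to −0.17 SD (20% lost).
- Among controls with slope −0.5, it shifts by +0.07 to +0.10 SD.
- Complete-case difference at admission: from −0.13 SD (controls unrelated, 15%) to −0.27 SD (controls opposite, 20%).
- After surgery, multiplied by 0.6: from −0.08 to −0.16 SD.

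A likelihood model on all records gave 0 within about 0.02 SD under these assumptions. A separate simulation used 30 per arm, SD 20, correlation 0.5, a true effect of −10, and more loss among highly stressed intervention patients. The complete-case estimate at the last visit averaged −11.5 and the mixed model −10.1, with Monte Carlo standard errors of about 0.25. If missingness follows the same pattern in both arms, the bias is near 0 and only precision is lost.

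**The case against.** The strongest reply has five parts.

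- **No analysis is labelled primary, and complete cases are never mentioned.** This is correct. The ANOVA is only the first-listed model, after Spearman correlations, and dropping incomplete patients follows from the method in its classical form. A separate analysis plan could add imputation, and the absence of a missing-data rule here is no fault. A reader might infer that the protocol flatly contradicts intention to treat by making a complete-case analysis its main one. The text does not support that. It supports a poor fit between the stated principle and the first model named.
- **The mixed model is already planned for every variable.** Also correct. A reader might infer from its position that it is reserved for surgery subgroups, but its specification gives an overall group comparison. The protection exists. What is missing is a statement that it decides, and that gap is made by the two models the protocol itself fixes.
- **Joint analysis of three scales is one reading.** The wording may mean one model per scale, so the figures above use only the four-visit case.
- **The sizes are pessimistic.** Missed questionnaires tend to cluster within patients, and only the last visit is remote, so independent misses probably overstate the loss. The detectable effects are for a single time point, not for a time × group test. At the protocol's own effect size of 1.20, power with 20 per arm is still 0.96. The post-surgery bias of 0.08 to 0.16 SD is about a quarter to a half of one standard error at 24 per arm (√(2/24) = 0.29 SD). All of this stands.
- **It is a feasibility trial.** The cost of a wrong choice is lower than in a confirmatory trial. Yet the first research question also asks how far the program affects stress, anxiety and pain, so the comparison will be read.

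**Conclusion.** The point holds as one of precedence and fit. The first group model for stress, pain and mood discards partial records in its classical form. A second model, filed under another question, estimates the same effect with those records kept. Nothing says which result counts. For HADS anxiety the mixed model is the only pooled group model, which is a further reason to let it decide.

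The size is illustrative. It rests on assumed missing rates of 5% to 10% per visit, independent across visits: 81% or 66% of patients retained (86% or 73% with baseline complete), and a detectable effect of about 0.83 or 0.91 SD in the four-visit case against 0.74 SD with no loss. A bias of about 0.1 to 0.25 SD needs missingness that depends on stress differently by arm, which the documents neither state nor exclude. The protocol's target effect of 1.20 is not threatened by the loss of precision. Confidence is high on the statistical principle and low on how much it will matter in this trial.

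The rule under Withdrawal From the Study, that a withdrawn participant's information is left out of the analysis, is a separate conflict with intention to treat. It would affect either model, and changing the model does not resolve it.

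**What to change.** In Data Analyses, state that conclusions on stress, pain, HADS anxiety and PANAS rest on the linear mixed model, fitted one outcome at a time to all available visits of patients as randomised. Relabel the split-plot ANOVA a complete-case sensitivity analysis. Reconcile the withdrawal rule separately, because as written it would also remove patients from the mixed model.

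No new data, patients or software are needed, since the mixed model is already planned for each variable. It relies on missing at random, a weaker assumption than the complete-case analysis makes. The change is not entirely free: the Results section says that recruitment is complete and the impact analysis is under way. The change should therefore be dated, with a note on whether any results had been seen, and both results should be reported.

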#### Experimental (Intervention) Group

The experimental group will receive a digital health solution during the first visit, and training on how to use this tool will be provided. Patients will take the digital health solution home with them and can use it as often as they like. The experimental group, after each 1 of the 4 standard care visits, will complete the same questionnaires as the control group.

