### Outcome Variables

#### Research Question 1 (Primary and Secondary Outcome Variables)

Stress, anxiety, and pain represent the primary outcome variables that will be measured using paper-and-pencil questionnaires.

The secondary outcome variables were overall quality of life, emotional status, mental well-being, self-efficacy perception, and patient activation during and after hospital stay.

To assess the primary outcome variables, the following questionnaires will be used after each standard care visit and will be administered by paper and pencil:

Patients’ and caregivers’ *self-reported stress* was measured using a VAS at enrollment (baseline), at admission for surgery, at hospital discharge, and 2 weeks after surgery. Operationally, a VAS is usually a horizontal line, 100 mm in length, anchored by word descriptors at each end, such as no stress versus highest stress possible [37].Patients’ *self-reported pain* was measured using a VAS for pain measurement at enrollment (baseline), at admission for surgery, at hospital discharge, and 2 weeks after the surgery. The VAS for pain is a validated single-item scale that is anchored by “no pain” (score of 0) and “pain as bad as it could be” or “worst imaginable pain” (score of 100). The VAS presents a high internal consistency, as shown by a Cronbach α of 0.9117 [38].Patients’*Hospital Anxiety and Depression Scale* (HADS) scores were measured at admission for surgery, at hospital discharge, and 2 weeks after surgery. The HADS consists of 2 dimensions with 7 questions each, one representing the anxiety subscale and the other representing depression, with both psychopathological concepts of anxiety and depression being independent. Each item was rated on a 4-point frequency scale, ranging from 0 to 3. The internal consistency of the HADS, as measured by the Cronbach α coefficient, was found to be .78 for the anxiety subscale and .86 for the depression subscale, indicating satisfactory reliability [39].

To assess the secondary outcome variables, the following questionnaires will be used after each standard care visit and will be administered paper and pencil:

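### Stress and pain are tested with baseline as an outcome time and without the stratification factors, and neither surgery analysis tests whether the effect differs by surgery

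*Protocol article*

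**What the plan says.** - **Model for stress, pain and PANAS.** Data Analyses states that they "will be subjected to a multivariate mixed analysis of variance (split-plot ANOVA", with time "as a within-subject factor (ie, 4 time points" and group as the only other factor.
- **What the four times are.** Stress is recorded "using a VAS at enrollment (baseline), at admission for surgery, at hospital discharge, and 2 weeks after surgery"; pain and PANAS follow the same schedule in Table 1. The intervention starts at the first of these: "The experimental group will receive a digital health solution during the first visit".
- **Stratification.** Randomization and Allocation says "The specific covariates in the clinical trial were represented by the type of surgery (3 surgeries) and sex". Neither factor appears in the ANOVA.
- **Other outcomes.** For mental well-being and HRQoL, both secondary, the same section does use the pre-measurement as a covariate.
- **Surgery type.** Two approaches are offered to explore how effects depend on surgery. In the first, "Data will be split for each of the surgeries, and variables will be analyzed individually using time and group" as factors. The second is a linear mixed model (LMM) for each variable, with time, group and time × group as fixed effects. Subjects and surgery "will be submitted as random factors", and age or sex is optional. The stated advantage is that "LMM allows for the flexible handling of unbalanced data, outliers, or missing observations without averaging the data of participants".
- **Analysis principle.** Intention to treat.

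**The concern.** Four features of the written models cost information or leave a stated question unanswered.

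1. No effect can be expected at baseline. Treating baseline as an outcome time pulls the group main effect towards zero and leaves the time × group test, on 3 degrees of freedom, to carry the treatment comparison.
2. Surgery type and sex were balanced by design but are not in the ANOVA. The variation they explain stays in the error term of the group comparison.
3. A split-plot ANOVA as usually run keeps only patients seen at every visit, which sits badly with intention to treat.
4. The question of whether the effect differs by surgery is addressed by separate analyses, which do not compare effects, and by a random surgery term, which only shifts outcome levels. With the three surgery types named under Randomization and Allocation, that variance would also rest on three units.

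At stake are the precision of the effect estimates that a feasibility trial hands to a definitive one, and whether the surgery question gets any answer.

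**Working it through.** **The plan's own figure.** Sample Size gives 30 per group for power 0.8, α .05 and effect size 1.20. A two-sided two-sample t-test at d = 1.20 needs 12 per group, so the figure does not reproduce; that is a separate matter. What counts here is that 30 per group has 99.5% power at 1.20 by a plain t-test and reaches 80% at d = 0.74. The article gives no power for the ANOVA.

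**Assumptions, not in the article.** Effect zero at baseline; SD 1 at each visit; equal correlation ρ between visits (0.3, 0.5, 0.7); complete data; one outcome at a time; two-sided 5%.

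**Noncentrality with 30 per arm** (30/2 = 15), constant effect D at the three later visits:

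- Group main effect over four times: the mean effect is (0 + D + D + D)/4 = 0.75D and its variance factor (1+3ρ)/4, so λ = 15(0.75D)² / [(1+3ρ)/4], F(1, 58).
- Time × group: λ = 15 × 0.75D² / (1−ρ), F(3, 174).
- Mean of later visits adjusted for baseline: λ = 15D² / [(1+2ρ)/3 − ρ²], F(1, 57).

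For D = 0.5 and ρ = 0.5: λ = 15 × 0.1406/0.625 = 3.375; 15 × 0.1875/0.5 = 5.625; 15 × 0.25/(0.6667 − 0.25) = 9.0.

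| D = 0.5 | ρ = 0.3 | ρ = 0.5 | ρ = 0.7 |
|---|---|---|---|
| Group main effect | 55% | 44% | 37% |
| Time × group | 35% | 48% | 72% |
| Baseline-adjusted mean | 82% | 84% | 93% |

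Relative to the adjusted analysis, the ratio of λ is 0.53/0.38/0.23 for the main effect and 0.48/0.63/0.78 for time × group. At D = 1.20 every cell is at least 97%.

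**Effects that change over time.** For effects e at the three later visits, time × group has λ = 15/(1−ρ) × [Σe² − (Σe)²/4]. The baseline-adjusted joint test over the three visits has λ = 15/(1−ρ) × [Σe² − ρ(Σe)²/(1+3ρ)]. Since ρ/(1+3ρ) never exceeds 1/4, the second λ is never smaller. At ρ = 0.5, with 171 error degrees of freedom for the joint test:

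| Effect at admission / discharge / 2 weeks | Time × group | Adjusted joint test | Adjusted mean |
|---|---|---|---|
| 0.5 / 0.5 / 0.5 | 48% | 70% | 84% |
| 0.8 / 0 / 0 | 90% | 92% | 35% |
| 0.8 / 0.4 / 0 | 87% | 92% | 66% |

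With an unstructured covariance the error degrees of freedom fall to about 55 and the joint test has 68%, 90% and 90%.

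**Strata left out.** Simulation of a single measurement with six strata of 10, exact 1:1 balance and 20,000 trials. When the strata explain 10%, 20%, 30% or 50% of the variance, the actual type I error of the unadjusted group comparison is 4.1%, 2.7%, 2.0% or 0.6%. Over the same range, power at d = 0.74 is 81–87% unadjusted and 84–98% adjusted. This concerns the between-patient comparison; a constant stratum shift cancels from time × group.

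**Complete cases.** With independent loss m at each of the three later visits, 60(1−m)³ = 51.4 at 5% and 43.7 at 10%.

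**Surgery.** Set side by side, the LMM has fixed terms for time, group and their interaction and a random surgery level. Nothing in it lets the group effect vary by surgery, so it returns one effect averaged over surgeries. The split-data analysis returns surgery-specific estimates with no test between them.

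**The case against.** The strongest reply has four parts.

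- **The time × group test is valid and conventional.** This stands. It is the usual test of difference in change, and the three-quarters dilution touches only the group main effect. Its 3 degrees of freedom also buy sensitivity to effects that vary over time: if the effect is confined to admission, it beats the averaged contrast by 90% to 35%. So it would be wrong to say that power is simply thrown away. The baseline-adjusted joint test keeps that sensitivity, however, and is ahead of time × group or practically level with it.
- **At the plan's own effect size the loss is negligible.** This stands for d = 1.20. It does not settle the matter, because a feasibility trial should also estimate smaller effects with useful precision.
- **An analysis that uses incomplete cases is already planned.** This stands. The LMM is to be run on each variable, so patients with a missing visit are lost only from the ANOVA, and only under its usual implementation. The article gives no missing-data rule, and an analysis plan not shown here may do so.
- **The surgery analyses are exploratory.** This stands, but an exploratory question still needs a term that addresses it.

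A reader might infer that the LMM as written already repairs the ANOVA and has merely been put in the wrong place. The text does not support that: the LMM has the same time and group terms, no baseline covariate and no restriction to post-baseline visits, and sex is optional. It improves on the ANOVA only in handling missing visits and taking in surgery level. Nor does the article name a main test; the ANOVA is the first group model listed after descriptive statistics and Spearman correlations.

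**Conclusion.** The point holds as a matter of efficiency and of an unanswered question. For a constant 0.5 SD effect with 30 per arm, the planned ANOVA tests have 35% to 72% power, against 82% to 93% for the baseline-adjusted mean, over correlations 0.3 to 0.7. The effect size, its constancy and the correlations are assumptions. For front-loaded effects the gain over time × group, now from the adjusted joint test, is small: 2 to 5 percentage points at correlation 0.5. At 1.20 there is no practical difference in power, only in precision. The ANOVA would use about 51 to 44 of 60 patients at an assumed 5% to 10% loss per later visit.

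A reader might also infer bias or too many false positives. The check shows neither: time × group stays valid, and leaving out the strata makes the group comparison conservative. On surgery type, neither planned approach tests whether the effect differs. The change should be made, because it costs little and the plan already adjusts two secondary outcomes for baseline.

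**What to change.** For each repeated outcome, fit an LMM to the post-baseline visits. Fixed effects: baseline value, visit, group, group × visit, surgery group and sex. Subject is random, or the visit covariance is unstructured. Report the group difference at each visit and averaged over visits, with 95% confidence intervals, plus the joint test across visits, so that the result does not depend on the effect being constant. Replace the split-data comparison with one group × surgery-group term, labelled exploratory, with surgery entered as fixed.

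If HADS is analyzed in this way, the article must first agree on whether it has a baseline: Table 1 schedules one, while the outcome description starts at admission.

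The cost is analysis wording and code, and a few degrees of freedom for the fixed factors. No data collection changes.
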